# A multicenter randomized clinical trial investigating the cost-effectiveness of treatment strategies with or without antibiotics for uncomplicated acute diverticulitis (DIABOLO trial)

**DOI:** 10.1186/1471-2482-10-23

**Published:** 2010-07-20

## Abstract

**Background:**

Conservative treatment of uncomplicated or mild diverticulitis usually includes antibiotic therapy. It is, however, uncertain whether patients with acute diverticulitis indeed benefit from antibiotics. In most guidelines issued by professional organizations antibiotics are considered mandatory in the treatment of mild diverticulitis. This advice lacks evidence and is merely based on experts' opinion. Adverse effects of the use of antibiotics are well known, including allergic reactions, development of bacterial resistance to antibiotics and other side-effects.

**Methods:**

A randomized multicenter pragmatic clinical trial comparing two treatment strategies for uncomplicated acute diverticulitis. I) A conservative strategy with antibiotics: hospital admission, supportive measures and at least 48 hours of intravenous antibiotics which subsequently are switched to oral, if tolerated (for a total duration of antibiotic treatment of 10 days). II) A liberal strategy without antibiotics: admission only if needed on clinical grounds, supportive measures only. Patients are eligible for inclusion if they have a diagnosis of acute uncomplicated diverticulitis as demonstrated by radiological imaging. Only patients with stages 1a and 1b according to Hinchey's classification or "mild" diverticulitis according to the Ambrosetti criteria are included. The primary endpoint is time-to-full recovery within a 6-month follow-up period. Full recovery is defined as being discharged from the hospital, with a return to pre-illness activities, and VAS score below 4 without the use of daily pain medication. Secondary endpoints are proportion of patients who develop complicated diverticulitis requiring surgery or non-surgical intervention, morbidity, costs, health-related quality of life, readmission rate and acute diverticulitis recurrence rate. In a non-inferiority design 264 patients are needed in each study arm to detect a difference in time-to-full recovery of 5 days or more with a power of 85% and a confidence level of 95%. With an estimated one percent of patients lost to follow up, a total of 533 patients will be included.

**Conclusion:**

A clinically relevant difference of more than 5 days in time-to-full recovery between the two treatment strategies is not expected. The liberal strategy without antibiotics and without the strict requirement for hospital admission is anticipated to be more a more cost-effective approach.

**Trial registration:**

Trial registration number: NCT01111253

## Background

Prevalence of diverticular disease increases with age, from less than 10% in people younger than age 40 to 50-66% in octogenarians, with similar frequency in men and women. Approximately three quarters of patients with diverticulosis remain asymptomatic throughout their lifetime. Asymptomatic disease is often an incidental finding during imaging or endoscopy for suspicion of colonic disorders. Of the 25% of patients who develop symptomatic diverticular disease, approximately three quarters develop diverticulitis [1,2]. Of all patients with diverticulitis, 75% have mild acute disease only and 25% develop complicated disease [3]. All and all about 5% of patients with diverticulosis will undergo an episode of complicated diverticulitis.

The cause of colonic diverticular disease has not yet been conclusively established. Epidemiologic studies have demonstrated associations between diverticulosis and diets that are low in dietary fiber and high in refined carbohydrates. Low intake of dietary fiber results in less bulky stools retaining less water and altering gastrointestinal transit time. These factors could increase intracolonic pressure (development of pressure zones that create diverticula alongside the vasa recta), and make evacuation of colonic contents more difficult [4]. Other factors that have been associated with an increased risk of diverticular disease include physical inactivity, constipation, obesity, smoking, and treatment with non-steroidal anti-inflammatory drugs [5,6].

Although much has been learned about the development of diverticula, less is known about the pathogenesis of diverticular inflammation. As discussed earlier, a minority of patients with diverticulosis will develop symptomatic disease. Initial theories of diverticulitis focused on ideas about the pathogenesis of appendicitis; a diverticulum lumen becomes obstructed by a faecolith leading to increased intradiverticular pressure and eventually causing inflammation. Interest has been generated in the role of altered peridiverticular colonic flora and low-grade chronic inflammation leading to periods of symptomatic disease, similar to periods of exacerbation and remission in inflammatory bowel disease [7].

The classical clinical presentation of diverticulitis in the western world includes left lower quadrant abdominal pain, tenderness, low-grade fever and leucocytosis. However, clinical features can be quite variable. Leucocytosis may only be present in 45-65% of the patients, and low-grade fever may be present in only 21% [8].

For a reliable diagnosis additional imaging is usually necessary. Computed tomography (CT) is recommended as initial radiological examination. Positive findings in ultrasound (US) are equally accurate in the diagnosis of diverticulitis. However CT has an advantage in excluding alternative diagnoses and visualising complications of acute diverticulitis needing intervention. For both US and CT, sensitivity is as high as 90%, with a specificity of up to 99% for CT [9].

The severity of diverticulitis is often graded with the use of modified Hinchey's criteria, based on CT imaging and on preoperative findings [10,11]. The Ambrosetti's criteria is based only on CT imaging, classifying in "mild" and "severe" diverticulitis. This classification system does not take into account the effects of coexisting conditions on disease severity or outcome [12]. (Table 1) Stage II disease is related to a large (> 5 cm) collection of pus, which is at distance (in the pelvis or the abdomen) of the sigmoid colon [10]. Stage II usually requires percutaneous drainage, while stages III and IV diverticulitis usually request surgery.

**Table 1 T1:** Hinchey classification and modified Hinchey classification of acute diverticulitis [10,12]

Hinchey	Modified Hinchey
	0 Mild clinical diverticulitis

I Pericolic abscess or phlegmon	1a Colonic wall thickening/Confined pericoloc inflammation
	
	Ib Confined small (< 5 cm) pericolic abscess

II Pelvic, intraabdominal, or retroperitoneal abscess	II Pelvic, distant intraabdominal, or retroperitoneal abscess

III Generalized purulent peritonitis	III Generalized purulent peritonitis

IV Generalized fecal peritonitis	IV Fecal peritonitis

Conservative treatment of mild diverticulitis usually includes careful observation, restriction of oral intake, administration of intravenous fluids, and most patients receive antibiotic therapy. The majority of patients with mild diverticulitis improve with these conservative measures. Less than 10% need percutaneous or operative treatment for disease progression and/or complications [13,14].

It is, however, uncertain whether patients with acute diverticulitis benefit from antibiotics, since evidence from prospective studies or randomized trials is lacking. In a recent review antibiotics are considered mandatory in the treatment of mild diverticulitis [15]. This advice lacks evidence and is based on experts' opinion only. Anaerobes are commonly isolated organisms in acute diverticulitis. Gram-negative aerobes, especially Escherichia coli, and facultative gram-positive bacteria, such as streptococci, are often cultured as well [16]. Therefore, broad-spectrum antibiotics are advised. Which antibiotic regimen should be used in diverticulitis is unclear [17,18]. There is scarse evidence that oral antibiotics are as effective as intravenous antibiotics [19].

Only one study has investigated the use of antibiotics in the treatment of acute uncomplicated diverticulitis. In a retrospective study by Hjern et al [20], there was no significant benefit from antibiotics in the treatment of mild diverticulitis. However, this study was hampered by selection bias due to its retrospective design and small patient groups.

Moreover, there is major discrepancy in the use of antibiotics between countries in Northwest Europe and other countries, including the United States and United Kingdom. In the Netherlands and Scandinavian countries antibiotic use for this disease is less common compared to these other countries, where antibiotics are considered mandatory. A Dutch survey showed that many gastro-enterologists prescribed antibiotics in the treatment of acute diverticulitis, but only a minority of Dutch surgeons did so [21]. In contrast, all UK surgeons responding to a survey prescribed antibiotics in the initial treatment of diverticulitis and 43% of them even for 7 days after hospital discharge [22].

Six professional organisations have issued formal guidelines concerning the use of antibiotics in uncomplicated diverticulitis. Five of these guidelines advice the use of antibiotics. (Table 2) [23-28]. Patients should start with intravenous antibiotics and after improvement within 2-4 days, oral antibiotics are continued to complete a 7-10 days treatment regimen. In the Netherlands, the Dutch Antibiotic Policy Committee considers antibiotics not primarily indicated in the treatment of uncomplicated diverticulitis [28].

**Table 2 T2:** Published guidelines and practise parameters

Organization	Year	Antibiotics Recommended	Original research cited	Which antibiotics	Original research cited	Route of administering	Original research cited
**American College of Gastroenterology**[23]	1999	Yes	None	Covering both Gram negative and anaerobes	Kellum [15]	Oral or intravenous, depending on clinical status	None

**European Association for Endoscopic Surgery**[25]	1999	Yes	None	Ciprofloxacin And Metronidazol	None	Oral or intravenous, depending on clinical status	None

**American Society of Colon and Rectal Surgeons**[24]	2006	Yes	None	Covering both Gram negative and anaerobes	Kellum [15]	Oral or intravenous, depending on clinical status	None

**Society of Surgery of the Alimentary Tract**[26]	2007	Yes	None	Broad spectrum antibiotics	None	Oral or intravenous, depending on clinical status	None

**World Gastroenterology Organization**[27]	2007	Yes	None	Covering both Gram negative and anaerobes	None	Oral or intravenous, depending on clinical status	None

**SWAB**[28]	2009	No, not primarily	None	Broad spectrum antibiotics	None	Oral or intravenous, depending on clinical status	None

Adverse effects of antibiotics are well known, such as allergic reactions and development of antibiotic resistance of bacterial species. The frequency of toxicodermia is 7-8% with the use amoxicillin, allergy reactions are accounted for in 1% of the patients, and the incidence of anaphylactic shock is 0,01-0,04% with the use of penicillin. Therefore, efforts are made to minimize the use of antibiotics in various fields in clinical medicine [29].

The lack of evidence for its use necessitates a scientific judgement of the role of antibiotics in the treatment of uncomplicated diverticulitis. Therefore, we initiated a randomized multicenter trial to investigate the effect of antibiotics on disease course in patients with mild acute diverticulitis.

## Methods/Design

### Objective

The main goal of the present study is to establish whether antibiotics are necessary in the primary treatment of acute mild diverticulitis, and whether a more liberal strategy without initial antibiotics is more cost-effective with respect to time-to-full recovery.

In daily practice there is an ongoing discussion about the relative benefits and disadvantages of a more conservative treatment strategy embracing the use of intravenous antibiotics. This strategy needs hospital admission and is, at least at the start, an in-hospital treatment regimen. A more liberal strategy, without antibiotics and without the strict requirement of hospital admission, may lead to a shorter hospital stay and reduced costs without compromising outcome.

Our hypothesis is that in uncomplicated (mild) acute diverticulitis, a liberal strategy treatment without antibiotics is a more cost-effective approach than conservative treatment strategy with hospital admission and antibiotics, outcome is measured by time-to-full recovery as primary outcome and diverticulitis-associated complication rates and patient well-being as secondary outcome.

### Study population

Inclusion criteria:

1. Only left-sided and primary (first attack) mild acute diverticulitis.

2. Diagnosis of diverticulitis by US and conditional CT. Diverticulitis-positive US findings are sufficiently accurate compared to CT findings [9]. In diverticulitis-negative US findings in clinically suspected patients, immediate i.v. contrast-enhanced CT is mandatory for confirmation of diverticulitis and exclusion of other pathology.

3) Staging of diverticulitis by CT. CT is needed for all patients for Hinchey/Ambrosetti classification (which is a CT-based classification system). In diverticulitis-positive US findings CT has to be performed within 24 hours. Staging diverticulitis is defined according the modified Hinchey/Ambrosetti staging. Only modified Hinchey stages 1a and 1b (1a Colonic wall thickening/Confined pericolic inflammation, 1b Confined small pericolic abscess) and Ambrosetti's "mild" diverticulitis stage are included. Figure 1 depicts a flow chart, showing the inclusion criteria and the steps after inclusion [10-12].

**Figure 1 F1:**
[figure not shown]
**Study flow chart**.

4. Informed consent.

Exclusion criteria are summarized in Table 3.

**Table 3 T3:** Exclusion criteria

1. Previous radiological (US and/or CT) proven episode of diverticulitis;
2. US and/or CT suspicion of colonic cancer

3. Inflammatory bowel disease (ulcerative colitis, Crohn's disease);

4. Hinchey stages 2, 3 and 4 or "severe" diverticulitis according to the Ambrosetti criteria, which require surgical or percutaneous treatment;

5. Other disease with expected survival of less than 6 months;

6. Contraindication for the use of the study medication (e.g. patients with advanced renal failure or allergy to antibiotics used in this study);

7. Pregnancy;

8. ASA (American Society of Anesthesiologists) classification > III;

9. Immunocompromised patient; (i.e., haematological malignancies, AIDS patients with low CD4+ counts, transplantation, chemotherapy, splenectomy, long-term corticosteroid use and genetic disorders such as severe combined immunodeficiency.

10. Clinical suspicion of bacteraemia (i.e. sepsis);

11. The ability of reading/understanding and filling in the questionnaires.

12. Antibiotic use in the 4 weeks prior to inclusion

### Study outline

Patients will be randomly allocated to one of the following two treatment strategies: Conservative strategy including immediate antibiotic treatment or liberal strategy without antibiotics (supportive measures only). (Table 4).

**Table 4 T4:** Treatment strategies

Conservative strategy with antibiotics	Liberal strategy without antibiotics
- Hospital admission;	- Admission only if discharge criteria are not met;

- Intravenous fluids and at least 48 hours of intravenous antibiotics and subsequently switch to oral antibiotics if tolerated (otherwise continuation i.v.) to complete a full 10-day treatment duration;	- No initial antibiotics;

- Adequate pain relief (VAS < 4);	- Adequate pain relief (VAS < 4);

- Oral intake as tolerated;	- Oral intake as tolerated;

- Daily monitoring.	- Daily monitoring when admitted to the hospital;

-Self monitoring at home after discharge -Out patient follow-up at regular intervals	- Self monitoring at home. - Out patient follow-up at regular intervals

In the conservative strategy, the use of antibiotics will be intravenously for at least 48 hours after which route of administration can be switched to orally if tolerated. Hospital admission in the liberal strategy is needed for patients with nausea and vomiting, in need of intravenous fluids or for patients with excessive pain not properly reacting to oral pain medication.

The interval between start of symptoms of the patient and administration of antibiotics will be registered. Also the period after inclusion and the actual first administration of antibiotics will be registered.

In both strategies CT is repeated in case of clinical deterioration. For patients in the liberal strategy treatment arm, clinical deterioration and/or proven subsequent complicated diverticulitis and/or other infectious foci (e.g., pneumonia, infections) may dictate start of antibiotic treatment, instigated by the treating physician. Criteria to start antibiotics in the liberal arm are temperature > 39°C, positive blood cultures and clinical suspicion of bacteraemia (i.e. sepsis). Criteria for sepsis are set by the American College of Chest Physicians and the Society of Critical Care Medicine. Two or more symptoms are required: Body temperature < 36°C or > 38°C, heart rate higher than 100 beats a minute, respiratory rate higher than 20 breaths a minute and white blood cell count < 4 × 10^9 ^or > 12 × 10^9 ^cells/L [31]. Also another infectious focus (e.g., pneumonia, urinary tract infections) may dictate start of antibiotic treatment, instigated by the treating physician.

The following discharge criteria are applied in both strategies: normal diet (defined by tolerating solid food and more than 1L of fluid orally), temperature < 38.0°C, VAS (Visual Analoge Score) pain score < 4 (with paracetamol only), self support as compared to the pre-illness level, and acceptance by the patient.

All outpatients will daily monitor and register their body temperature. Written and oral instructions at discharge are given, and relevant telephone numbers and contact information will be provided. In case of fever above 38˚C, progression of pain above a VAS of 4 or other clinical signs of deterioration, patients can contact the hospital or emergency department immediately.

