### Endpoints

The primary endpoint is time-to-full recovery within a follow-up period of 6 months. Full recovery is defined by the following criteria: discharged from the hospital (out-patient), normal diet (defined by tolerating solid food and more than 1L of fluid orally), temperature < 38.0°C, and VAS pain score < 4, no use of daily pain medication or back to pre-illness pain medication use, and resuming to pre-illness working activities; as assessed by questionnaires and out-patient clinic visits.

The secondary endpoints are: proportion of patients who develop complicated diverticulitis require surgery or non-surgical intervention; number of days outside the hospital in a 6 months period; direct and indirect medical costs at 6 months follow-up; occurrence of complicated diverticulitis defined as abscess, perforation, stricture and/or fistula; predefined side-effects of initial antibiotic treatment (e.g. antibiotic resistance/sensitivity pattern, allergy); morbidity (e.g. pneumonia, myocardial infarction, urinary tract infection); mortality; readmission rate within 6 months and acute diverticulitis recurrence rates at 12 and 24 months follow-up. Changes in health status and valuation over time will be measured using generic and disease specific quality of life questionnaires (Euro-Qol 5D, Short Form 36 (SF-36) and the Gastro-Intestinal Quality of Life Index (Giqli)) on admission and after 3, 6, 12 and 24 months.

A recurrence is defined as ultrasound- or CT-proven acute diverticulitis after complete resolution of symptoms more than 1 month after initial discharge from hospital. If a patient dies during follow-up, the reason for death will be recorded as related or unrelated to diverticular disease.

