### Randomization

Computerized block randomization for allocation of treatment group, stratified for center and for Hinchey 1a and 1b, will take place after all inclusion and exclusion criteria have been verified and informed consent has been obtained. A standardized case record from (CRF) will be used. This CRF is partially web-based via a secured internet module. A minimum of 10% of the CRF data will be verified with source data by an independent audit.

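### The first quality-of-life assessment is tied to hospital admission, which is compulsory in one arm only; it should be tied to consent and randomisation (minor)

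*Protocol article*

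**What the plan says.** **Timing of quality of life.** The Endpoints section of the protocol article measures change in health status and valuation with the EQ-5D, SF-36 and Giqli, "on admission and after 3, 6, 12 and 24 months". No other first time point is given.

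**Admission by arm.** Table 4 (Study outline) lists hospital admission as part of the conservative strategy. For the liberal strategy it says "Admission only if discharge criteria are not met". The Discussion confirms that admission is not mandatory for liberal-arm patients who fulfil those criteria at study entry.

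**Order of events.** Randomisation "will take place after all inclusion and exclusion criteria have been verified and informed consent has been obtained". The article does not place admission or the first questionnaire before or after that step. Safety monitoring states that neither patient nor treating physician is blinded.

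**Use of the scores.** Change over time is listed with the secondary endpoints. The Economic evaluation section names cost per QALY gained among its main analyses.

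**Timing of antibiotics.** The Study outline also states: "The interval between start of symptoms of the patient and administration of antibiotics will be registered". The next sentence reads: "Also the period after inclusion and the actual first administration of antibiotics will be registered". Neither interval is called a baseline variable or given an analysis.

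**The concern.** A baseline should be taken at the same point in both arms, before anything that depends on the allocation. Admission does not meet that test here, because one strategy requires it and the other is designed to avoid it where possible. If sites follow the text, three things can happen:

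- Liberal-arm patients who are never admitted have no baseline form.
- A liberal-arm patient who goes home and is admitted later completes the form when the illness has worsened, well after randomisation.
- In either arm, the form may be completed by a patient who already knows the allocated strategy.

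The first gap would not be random. Patients who skip admission are those who already tolerate a normal diet, have no fever, have controlled pain and can look after themselves. Observed baselines would then cover the whole conservative arm but only the sicker part of the liberal arm. At stake are the change scores and the QALY comparison, in a trial whose title announces a cost-effectiveness question.

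**Working it through.** There is no figure in the plan to reproduce. The check sets the passages side by side and then gauges the size.

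**Step 1: does the stated time point exist for each patient?**

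| Patient | Admission under the plan | First assessment as written |
|---|---|---|
| Conservative arm | Required | Exists; order relative to allocation not stated |
| Liberal arm, discharge criteria not met at entry | Yes | Exists; order relative to allocation not stated |
| Liberal arm, criteria met at entry, never admitted | No | Does not exist |
| Liberal arm, criteria met at entry, admitted later | Later, on deterioration | Exists, but after randomisation and at a worse point in the illness |

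The last two rows occur only in the liberal arm. The later time points inherit the problem: if months are counted from admission, the third row has no origin. The primary endpoint, by contrast, is counted from randomisation in both arms (Sample size calculation).

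**Step 2: direction.** Let *f* be the share of liberal patients with no baseline form, and *d* the amount by which their true baseline utility exceeds that of the admitted liberal patients. If *u* is the mean utility of the admitted, the true arm mean is (1 − *f*)*u* + *f*(*u* + *d*) = *u* + *fd*. An analysis of available forms sees only *u*, so the liberal baseline is understated by *g* = *fd*. The article gives neither *f* nor *d*. With *g* > 0, the liberal arm's gain from baseline looks too large, while its area-under-the-curve QALY looks too small. The two outcomes would be biased in opposite directions.

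**Step 3: size for the QALY (illustration).** The article does not state how QALYs are computed. Assume the trapezoidal rule over the 6-month period used for costs, with scores at 0, 3 and 6 months (0, 0.25 and 0.5 years):

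QALY = 0.25 × (u0 + u3)/2 + 0.25 × (u3 + u6)/2 = 0.125·u0 + 0.25·u3 + 0.125·u6

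- Share of the total weight on the first score: 0.125 / 0.5 = 25%.
- Assumed *g* = 0.05: 0.125 × 0.05 = 0.00625 QALY.
- Assumed *g* = 0.20: 0.125 × 0.20 = 0.025 QALY.

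The spurious shift in the QALY difference is therefore about 0.006 to 0.025 over that assumed range. A longer horizon leaves the absolute shift unchanged, since the weight on the first score stays at 0.125, but makes it a smaller share of the total.

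**The case against.** The best reply is that study entry was meant. In hospital trials the admission visit is often shorthand for the inclusion visit. This is a condensed article, the flow chart is not reproduced in the text available, and the case record form may well state the timing for outpatients. Nothing says that sites would skip the form for a patient who goes home. Nor does the article show that any baseline is completed after allocation: a patient may already be in hospital while awaiting the staging CT, since "In diverticulitis-positive US findings CT has to be performed within 24 hours", and so complete the form before randomisation. All of this stands, and it keeps the point minor. It does not remove the point, because the article does not leave the timing open. It states an anchor, and that anchor exists by design for all of one arm and only part of the other.

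A reader might infer more: that symptom duration is likewise undefined for half the patients, because the liberal arm receives "No initial antibiotics" and both registered intervals end at an antibiotic dose. The documents do not support that.

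- The two intervals read as measures of treatment delay, which naturally apply to patients given antibiotics. For liberal patients, later events "may dictate start of antibiotic treatment, instigated by the treating physician", and the intervals then describe that later treatment.
- A condensed article need not list every case-record item, so the date of symptom onset may be recorded for everyone.
- Illness duration and any wait for the CT precede randomisation, so they are balanced between arms in expectation. Spread between patients does not use up a 5-day margin, which is a difference between arms in median recovery time.
- Adding symptom duration to the Cox model is a debatable choice, not a correction. The margin is a hazard ratio derived from unadjusted medians, and an adjusted hazard ratio is generally a different quantity.

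**Conclusion.** The point holds for quality of life only, and it is minor. As written, the first EQ-5D, SF-36 and Giqli assessment depends on an event that is compulsory in the conservative arm and conditional in the liberal arm, and it is not placed before the open-label allocation. Change in health status and cost per QALY can be biased as a result. The primary endpoint is not affected: it runs from randomisation and uses no baseline quality-of-life score.

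The size cannot be fixed from the article, because the share of liberal patients never admitted and their utilities are not given. The shift of about 0.006 to 0.025 QALY rests on an assumed trapezoidal calculation and an assumed utility gap of 0.05 to 0.20. It also supposes that sites follow the wording literally and that missing baselines are not dealt with in the analysis. If sites in fact collect the form at inclusion in both arms, before allocation is known, the bias disappears and only the wording needs correcting.

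**What to change.** In the Endpoints section, replace the admission anchor with *after informed consent and before randomisation*, for all patients in both arms, and state that 3, 6, 12 and 24 months are counted from randomisation. Who is admitted and how patients are treated stay as they are.

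The cost is one change of wording plus an instruction to sites. The small downside is practical: acutely ill patients must complete three questionnaires before the allocation is revealed. No change to the symptom-onset or antibiotic intervals, or to the Cox model, is needed on this account.
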